### Blinding

Blinding is not able to be performed as it is not possible to formulate identical-appearing preparations of HIP and slow-release iron. The controlled release iron tablets are too large to enclose in capsules and cannot be cut or ground. Consequently, the study will follow an open label design. An individual patient's participation in the study will cease at the end of the 6 month study period. If, before this time, the patient experiences severe anaemia (<65 g/L), symptomatic anaemia or the patient's attending physician believes that additional therapy is required (eg blood transfusion), they will be considered to have reached an end-point and will be withdrawn from study medication, but will still be followed up, with outcomes measured.

### Outcome measures

The primary outcome measure will be the difference in TSAT values between the HIP and ferrous sulphate groups at the end of the 6 month study period.

The secondary outcome measures will be the differences between the 2 groups at the end of the 6 month study period with respect to serum ferritin concentration, haemoglobin level, DPO dosage, Key's index (DPO dosage divided by haemoglobin) and incidence of adverse events.

### Procedures

Patients will take 2 tablets (HIP or ferrous sulphate) nocte for a period of 6 months. They will be instructed to take their study medications on an empty stomach and at least 2 hours apart from phosphate binder ingestion. At the time of inclusion in the study, demographic and clinical data will be recorded. All patients will be allowed their usual diet during the study period. DPO dosages will modified according to unit protocols, based on haemoglobin level. Full blood counts will be measured monthly, as per usual clinical practice. Iron studies will be measured every 2 months, as usual clinical practice. Patients will receive a medical review by their nephrologists every 2 months, as per usual clinical practice. No other procedure will be undertaken and all other care (including blood tests) will be provided according to standard unit protocols. Figure 2 outlines the trial schedule.

**Figure 2 F2:**
[figure not shown]
**Trial schedule (all tests are ordered as per routine clinical practice)**.

An individual patient's participation in the study will cease at the end of the 6 month study period. If, before this time, the patient experiences severe anaemia (<65 g/L), symptomatic anaemia (e.g. new onset or worsening shortness of breath or ischaemic chest pain attributable to the low haemoglobin) or the patient's attending physician believes that additional therapy is required (eg blood transfusion), they will be considered to have reached an end-point and will be withdrawn from study medication, but will still have blood counts measured monthly and followed for study outcomes. A patient's participation in the study will also cease if, during the course of the study, they complete PD therapy (eg renal transplantation or conversion to haemodialysis).

### Adverse Events

The number and proportion of subjects who report treatment-emergent adverse events will be summarized for each treatment group. Treatment emergent events include events that start on or after Day 0 of the study [that is the first day of Study Drug administration], and were not present at baseline, or were present at baseline, but increased in severity after the start of the study. The Medical Dictionary for Regulatory Activities [MedDRA] Terminology will be used to classify all adverse events with rESAect to System Organ Class [SOC], high level group term (HLGT), and preferred term.

For the purposes of this study, anaemia (serum Hgb or Hct below the normal range or worsened from baseline) will not be considered an adverse event unless it reaches a severe level (<65 g/L) or is associated with significant symptoms. Similarly, iron deficiency (iron indices below the normal range or worsened from baseline) will not be considered an adverse event.

### Sample size calculations

Prospective power calculations indicate that the study will have adequate statistical power (80% probability) to detect a clinically significant increase in TSAT of 7%, assuming α = 0.05 and a population standard deviation of 8%, if 44 patients were recruited in the study (22 in each group). Allowing for a 15% drop-out rate over 6 months using the adjustment formula of 1/[1 - drop-out rate] ^2^, we aim to recruit a total of 60 patients (30 in each group). We anticipate that a recruitment period of 18 months will be required. The assumptions for these power calculations were based on a previous randomised controlled trial of oral versus intravenous iron supplementation in PD patients [8], in which the baseline values were 107 ± 3 g/L for haemoglobin, 24.2 ± 1.7% for transferrin saturation and 323 ± 46 μg/L for serum ferritin concentration. Based on these assumptions, we estimate the power of the study for secondary outcome measures to be 77% for serum ferritin (δ 150 μg/mL, σ 180 μg/mL), 62% for haemoglobin (δ 7 g/L, σ 10 g/L), 22% for DPO divided by haemoglobin (δ 0.00075 μg.L/kg.g/week, σ 0.002 μg.L/kg.g/week) and 93% for the occurrence of gastrointestinal events (HIP 8% vs ferrous sulphate 46%).

The assumptions used for the power calculations are conservative and based on our previous study in 28 PD patients [22] and that of Nissenson et al in 37 haemodialysis patients ^1^. Because of power considerations and the relatively short duration of the study, no interim analysis is planned.

### Statistical analysis

#### Primary Outcome Analyses

Differences between the intervention and control groups with respect to the primary outcome measure (TSAT level at 6 months) will be measured by comparison of the mean TSAT in each group, adjusted for baseline values (analysis of covariance). Data will be analysed on an intention to treat basis. For patients withdrawing before the end of the 6 month study, their TSAT at the time of withdrawal will be taken as their final haemoglobin.

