### Study design

The study is a prospective, open-label, randomised controlled trial. Patients will be randomised to one of two treatment groups in equal proportion (Figure 1). To ensure adequate concealment of allocation, the randomisation will be performed using sequentially numbered, opaque, sealed envelopes, stratified for the presence or absence of a TSAT ≤ 20%. The sequence of interventions was obtained from a computer-generated random number list in permuted blocks provided through the Australasian Kidney Trials (AKTN) network.

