#### Secondary Outcome Analyses

Secondary analysis will be performed by repeated measures analysis of covariance with and without adjustment for baseline characteristics. The analyses used for secondary outcome measures will include unpaired t-test (serum ferritin, Key's index), Mann-Whitney U-test (DPO dosage) and chi square test (adverse drug reactions).

Categorical baseline characteristics (e.g. sex, race, comorbid illnesses, etc.) will be summarized with the number and percent of subjects in each treatment group with the characteristic. Quantitative characteristics (e.g., age and weight) will be summarized by mean and standard deviation or median [interquartile range], depending on data distribution. The number and percent of subjects who are randomised, treated with randomized Study Drug, require intervention, prematurely discontinue, and complete the study will be summarized. Fisher's exact test or the Chi-square test will be used to assess treatment group differences in the proportions of subjects who require intervention and who complete the study. The number and percent of subjects will be summarised for each reason for premature discontinuation.

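### The simple secondary tests ignore the TSAT ≤ 20% stratum used in randomisation, and baseline values; this is conservative and costs some precision

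*Protocol article*

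**What the plan says.** Study design: allocation is 1:1, taken from a "computer-generated random number list in permuted blocks", and is "stratified for the presence or absence of a TSAT ≤ 20" per cent. This is the only stratification factor stated.

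Primary Outcome Analyses: the 6-month TSAT is analysed by "comparison of the mean TSAT in each group, adjusted for baseline values (analysis of covariance"). The stratum is not named and no functional form is given for the baseline term.

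Secondary Outcome Analyses gives two things. The first is a "repeated measures analysis of covariance with and without adjustment for baseline characteristics", with no list of covariates. The second is a set of named tests: "unpaired t-test (serum ferritin, Key's index), Mann-Whitney U-test (DPO dosage) and chi square test (adverse drug reactions"). Haemoglobin is not assigned to any of the named tests.

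**The concern.** Stratified permuted blocks hold the arms close to balance on the TSAT ≤ 20% factor. If that factor predicts an outcome, between-stratum variation is largely removed from the difference between arms. A test that ignores the stratum still counts that variation as noise. Its reported standard error is then larger than the true one, it rejects a true null less often than 5%, and it wastes precision that the design has already gained.

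A link between the stratum and some of these outcomes is plausible, since ferritin and TSAT are both iron indices. The trial is small, and the article's own power is 77% for ferritin and 22% for the DPO-to-haemoglobin ratio, so precision is worth keeping. The named tests are also a stated choice that does not match the stated design. They are not simply a detail left for a later document.

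**Working it through.** **Inputs from the article (Sample size calculations).** 22 per arm evaluable; α 0.05, taken as two-sided; TSAT δ 7 and SD 8; ferritin δ 150 and σ 180; mean baseline TSAT 24.2%.

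**Assumptions, not in the article.** The share of outcome variance explained by the stratum (R² = r²); block size 4; about 30% of patients at or below 20%, from Φ((20 − 24.2)/8) = Φ(−0.525) = 0.30.

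**1. The plan's own figures.** For a two-sample t-test with n = 22 per arm, the non-centrality is (δ/σ)·√(n/2) = (δ/σ)·√11.
- TSAT: (7/8)·3.317 = 2.90, power 80.9% (stated 80%).
- Ferritin: (150/180)·3.317 = 2.76, power 77.0% (stated 77%).
- DPO/haemoglobin: (0.00075/0.002)·3.317 = 1.24, power 22.9% (stated 22%).
- Drop-out: 44/0.85² = 60.9 (stated 60).

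These reproduce, the last to within one patient, so 22 per arm is the right basis.

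**2. Unpaired t-test after stratified randomisation.** The true SE is about √(1 − R²) times the reported SE. The excess is therefore 1/√(1 − R²) − 1, and the actual two-sided α is about 2·[1 − Φ(1.96/√(1 − R²))].

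| Assumed R² | SE too wide by | Actual α |
|---|---|---|
| 0% | 0% | 5.0% |
| 5% | 2.6% | 4.4% |
| 10% | 5.4% | 3.9% |
| 20% | 11.8% | 2.8% |

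Simulation (22 per arm, blocks of 4) agrees: actual α of about 4.6, 3.8 and 2.7% at R² of 5, 10 and 20%.

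**3. Ferritin power, like for like.** Both tests must be evaluated after stratified allocation, because that allocation also raises the actual power of the t-test slightly above 77%. Simulation with 40,000 runs:

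| Assumed R² | t-test | With stratum | Gain (points) |
|---|---|---|---|
| 5% | 77.6% | 79.1% | about 1.5 |
| 10% | 77.9% | 80.9% | 3.0 |
| 20% | 79.2% | 85.6% | 6.4 |

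At R² = 0 adding the stratum brought no loss. These gains are for the stratum alone; adjustment for the outcome's own baseline is a separate gain and is not counted here.

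**4. Mann-Whitney and chi-square tests.** The same argument gives the same direction. No size was calculated for them.

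**5. Primary ANCOVA.** The model was simulated with and without the stratum for four baseline shapes (linear, step at 20%, hinge, quadratic) at three strengths (0.3, 0.5, 0.7), with 4,000 runs under the null and 2,000 at δ = 7. Without the stratum, type I error was 0.037 to 0.057 across the 12 scenarios and absolute bias was below 0.1 TSAT points. The effect on power of adding the stratum was:
- linear or hinge: about 1 point or less either way (for example 91.1 to 90.2%, and 86.1 to 86.2%, at strength 0.5);
- quadratic: 0 to 2.4 points gained;
- pure step at 20%: 0.8, 2.5 and 5.1 points gained at strengths 0.3, 0.5 and 0.7.

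**The case against.** The best reply is that the secondary plan also contains a repeated measures ANCOVA adjusted for baseline characteristics. That model may include baseline TSAT or the stratum, and a covariate list is commonly left to the full protocol or SAP. This stands in part: it would be wrong to say that nothing in the secondary plan can absorb the stratum. But the same sentence also plans an unadjusted version, and the three simple tests are named outright and cannot be adjusted at all. For haemoglobin the reply stands fully. No t-test is assigned to it, so no loss can be claimed there on this ground.

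A second reply is that the size rests wholly on an assumed association. That is true. At r = 0.1 to 0.2 the SE excess is only 0.5 to 2%, and actual α is 0.049 to 0.046.

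Three stronger readings are tempting, and the article does not support them.
- A reader might infer that the primary analysis depends on a strictly linear baseline effect. The stratum is a cut of a covariate that the model already contains, and under 1:1 randomisation ANCOVA stays valid when the shape is wrong. Only some precision can be lost.
- A reader might infer that stratifying at 20% implies a different treatment response below it. The article gives no such rationale, and balancing a prognostic factor is reason enough to stratify. A main-effect stratum term would not model a different response in any case.
- A reader might credit the fix with the whole rise from the stated 77% for ferritin. Part of that rise comes from the stratified allocation itself.

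**Conclusion.** The point holds for the t-test, Mann-Whitney test and chi-square test named for secondary outcomes. They do not use the randomisation stratum, and the tests of ferritin, Key's index and DPO dosage do not use baseline values either. For the t-tests, with the stratum explaining an assumed 0 to 20% of outcome variance, standard errors are 0 to about 12% too wide, actual α runs from 5% down to about 3%, and the ferritin power forgone is 0 to about 6.5 points. The error is always in the conservative direction: it does not inflate false positives or bias the estimates. The planned repeated measures ANCOVA may cover part of it, but lists no covariates.

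The primary ANCOVA is valid as written. Adding the stratum there is optional, worth roughly −1 to +5 points of power depending on an assumed baseline shape. Overall this is a minor, nearly free improvement.

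**What to change.** In Secondary Outcome Analyses:
- for serum ferritin and Key's index, replace the unpaired t-tests with ANCOVA of the 6-month value on arm, the outcome's own baseline and the TSAT ≤ 20% stratum;
- for DPO dosage, replace the Mann-Whitney test with a van Elteren (stratified rank) test;
- for adverse drug reactions, replace the chi-square test with a Mantel-Haenszel test by stratum;
- for the repeated measures ANCOVA, state that the stratum is in the model.

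Naming the stratum in the primary ANCOVA is optional.

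The cost is wording, about one degree of freedom per model for the stratum, and one more where the outcome's own baseline is added. The stratum is already recorded for randomisation. The change should be made before outcome data are seen.

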### Concurrent Treatments

Vitamin B and folic acid supplementation are permitted. Vitamin C supplementation, melatonin and androgen therapy are prohibited during the study period.

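### The withdrawal rule for the primary endpoint names the wrong variable, leaves its scope unclear and carries one earlier TSAT forward as the 6-month result, which can bias the TSAT difference

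*Protocol article*

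**What the plan says.** Under Primary Outcome Analyses the protocol defines the "primary outcome measure (TSAT level at 6 months"), compares groups by analysis of covariance adjusted for baseline, and states: "Data will be analysed on an intention to treat basis". The next sentence is the only handling of incomplete primary data: "For patients withdrawing before the end of the 6 month study", "their TSAT at the time of withdrawal will be taken as their final haemoglobin".

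Two other places describe what happens after treatment is stopped for severe anaemia, symptomatic anaemia or a perceived need for additional therapy. Under Blinding, such patients "will be withdrawn from study medication, but will still be followed up, with outcomes measured". Under Procedures, after Figure 2, they "will be withdrawn from study medication, but will still have blood counts measured monthly and followed for study outcomes". The same paragraph says that participation ceases for patients whose peritoneal dialysis ends, for example through transplantation or a move to haemodialysis. Procedures also sets iron studies at 2-month intervals.

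**The concern.** There are three defects in one sentence.

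- **Wrong variable.** A rule for TSAT assigns its value to haemoglobin, a secondary outcome. Read literally, it cannot be applied to the primary analysis.
- **Unclear scope.** The sentence does not say whether *withdrawing* means stopping study medication or leaving the study. On the first reading it puts an earlier value in place of a 6-month TSAT that the protocol says will be measured, directly after promising intention to treat.
- **Carry-forward as the primary method.** On either reading, TSAT is assumed to freeze at its last measured level, and the imputed value is analysed as if observed.

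At stake is the estimate of the primary endpoint. With 60 patients planned and 15% drop-out assumed, about 9 values (60 × 0.15) would be handled by this rule. Leaving its scope open in an open-label trial also means that the choice could be made after results by arm are known.

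**Working it through.** **1. The passages side by side.** Blinding and Procedures use *withdrawn* only for stopping medication, with follow-up continuing. Procedures uses *cease* for the end of participation. If Primary Outcome Analyses uses the word in the same sense, its rule collides with the follow-up described in those two sections. If it means leaving the study, there is no collision. The text does not settle which.

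**2. Age of the carried value.** Iron studies are at months 0, 2, 4 and 6. A TSAT at withdrawal can therefore be up to 2 months old. For someone withdrawing before month 2 it is the baseline value itself, so the outcome equals the covariate and the recorded change is zero.

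**3. The plan's own figures.** From Sample size calculations: difference 7 points, SD 8, α 0.05 (taken as two-sided), 22 per arm, 15% drop-out. The noncentral t gives 80.9% power at 22 per arm. The inflation is 44/0.85² = 60.9, against the stated 60. The sample size reproduces and is not in dispute.

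**4. Illustration with a true effect.** Let *d* be the share withdrawing in each arm and *f* the share of the effect reached at the carried value. If patients who withdraw would still show the full effect at month 6, the expected estimate is 7 × [1 − d(1 − f)]. Assume linear build-up and a last TSAT equally likely at month 0, 2 or 4, so the mean of *f* is 1/3.

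- d = 15% (the protocol's drop-out rate): 7 × (1 − 0.15 × 2/3) = 6.30
- d = 25% (the rate the Background gives for the earlier haemodialysis study): 7 × (1 − 0.25 × 2/3) = 5.83
- Range for *f* from 0 to 2/3: 5.95 to 6.65 at 15%, and 5.25 to 6.42 at 25%

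The benchmark matters:

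| State of the effect after stopping | Carry-forward (15% / 25%) | Observed month-6 value (15% / 25%) |
|---|---|---|
| Still builds to 7 | 6.30 / 5.83 | 7.00 / 7.00 |
| Stays at its level on stopping | 6.30 / 5.83 | 6.30 / 5.83 |
| Lost entirely: 7 × (1 − d) | 6.30 / 5.83 | 5.95 / 5.25 |

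In the second row carry-forward costs nothing relative to observed values. In the third it overstates the effect that intention to treat would estimate.

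**5. Illustration with no true effect.** If both arms share a common 6-month change *c*, the bias (HIP minus ferrous sulphate) is c × (1 − f) × (d_FS − d_HIP). With mean *f* = 1/3:

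- Equal withdrawal: 0
- c = 6, 20% vs 10%: 6 × 2/3 × 0.10 = 0.4
- c = 2, 35% vs 10%: 2 × 2/3 × 0.25 = 0.33
- c = 6, 35% vs 10%: 6 × 2/3 × 0.25 = 1.0

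Simulating the ANCOVA with 30 per arm, SD 9 and within-patient correlation 0.6 agrees with these biases. Two-sided type I error is about 8% in the last scenario (above 9% at the protocol's SD of 8) and about 5 to 5.6% in the two milder ones. The sign follows the drift and reverses if *c* is negative or the imbalance is the other way round.

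**The case against.** The best defence is that *withdrawing* refers only to patients who leave the study. Then nothing observed is overridden, and Blinding, Procedures and Primary Outcome Analyses agree. That reading is possible, so a reader who infers that observed 6-month values will certainly be discarded goes beyond the text. What remains is the ambiguity, the wrong variable and carry-forward as the primary method.

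A reader might also infer that withdrawal is bound to be heavier on ferrous sulphate, because Sample size calculations expects gastrointestinal events in 46% against 8%. Those are event rates, not withdrawal rates. The listed triggers for stopping medication are anaemia or need for additional therapy, and the only drop-out figure planned is 15% overall. The 35% vs 10% split, the 6-point drift, the correlation of 0.6 and the SD of 9 are assumptions with no source in the document.

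Power is not the issue either. With all 60 analysed and an expected estimate of 6.3 points, power at SD 8 is 85.1%, above the 80% target. Finally, the details of a mixed model commonly belong in an analysis plan that is not shown. That is fair for the detail, but here the protocol itself fixes the primary rule, and fixes it badly.

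**Conclusion.** The point holds in a limited form. The sentence is wrong as written (haemoglobin for TSAT), its scope conflicts with the protocol's own use of *withdrawn* or is at best undefined, and it makes single-value carry-forward the primary method. It **can** bias the 6-month TSAT difference; neither size nor direction follows from the document.

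Under the assumptions shown, the loss on a true 7-point effect is about 0.7 points at 15% withdrawal and 1.2 at 25%, but only if the effect would have persisted and kept building after stopping. If it stays at its level on stopping, there is no loss relative to observed values. With no true effect, the bias is zero under equal withdrawal, 0.3 to 0.4 points under modest imbalance or drift, and about 1 point in the strongly unbalanced case. The case for change rests on the textual defects and the cheap remedy, not on a demonstrated bias.

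**What to change.** Reconcile Blinding, Procedures and Primary Outcome Analyses, and replace the withdrawal sentence with wording such as:

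*All randomised patients are analysed in their allocated group. The observed 6-month TSAT is used whether or not study medication was stopped. Where it is missing, for example after transplantation or conversion to haemodialysis, the 6-month treatment difference is estimated from a mixed model for repeated measures on TSAT at months 2, 4 and 6, with baseline TSAT by visit and treatment by visit. Carrying forward the TSAT at withdrawal is a sensitivity analysis only.*

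Settle this before outcome data are examined by arm. No dose or stopping rule is touched, and no extra test is needed because 2-monthly iron studies are already routine care. The costs are a slightly more complex model and the chance that values taken after discontinuation dilute an on-treatment effect (5.95 rather than 6.30 points at 15% withdrawal if the effect is wholly lost). That dilution belongs to the intention-to-treat question the protocol says it is asking.
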